## Abstract

**Background:**

Due to the increase of cardiovascular diseases acetylsalicylic acid (ASA) has become one of the most frequently prescribed drugs these days. Despite the rising number of patients with ASA medication presenting for elective general and abdominal surgery and the potentially increased risk of hemorrhage in these patients, there are no clear, evidence-based guidelines for the perioperative use of antiplatelet agents. The present randomised controlled trial was designed to evaluate the safety and optimize the use of ASA in the perioperative management of patients undergoing general and abdominal surgery.

**Methods/Design:**

This is a two-arm, monocenter randomised controlled trial. Patients scheduled for elective surgical treatment (i.e. inguinal hernia repair, cholecystectomy and colorectal resections) with ASA as a permanent medication are randomised equally to perioperative continuation or discontinuation of ASA. Patients who are randomised in the discontinuation group stop the administration of ASA five days prior to surgical treatment and start intake of ASA on postoperative day 5. Fifty-two patients will be enrolled in this trial. The primary outcome is the incidence of postoperative bleeding and cardiovascular events at 30 days after surgery. In addition a set of general as well as surgical variables are analysed.

**Discussion:**

This is a randomised controlled two-group parallel trial designed to assess the safety and optimize the use of ASA in the perioperative management of patients undergoing general and abdominal surgery. The results of this pilot study build the basis for a confirmative randomised controlled trial that may help to clarify the use and potential risk/benefits of perioperative ASA medication in patients undergoing elective surgery.

**Trial registration:**

The trial is registered with Current Controlled Trials ISRCTN45810007.

## Background

The individual risk for perioperative bleeding in abdominal and general surgery is influenced by multiple factors. Such factors include extent and type of surgery as well as patient-related features such as age, co-morbidities and perioperative medication. Considering the current demographic development surgeons are being confronted with older patients presenting with multiple co-morbidities and medications. Antiplatelet agents and in particular acetylsalicylic acid (ASA) were shown to be beneficial in a variety of atherothrombotic diseases [1-4] and are therefore among the most frequently prescribed drugs these days. However, due to the increased risk of hemorrhage the perioperative use of ASA has remained an issue of ongoing discussion [5-13].

Randomised controlled trials (RCT) that allow evidence-based recommendations regarding the perioperative use and risk of ASA in general and visceral surgery are still lacking. Therefore, the decision to balance possible thromboembolic risks after withdrawal of ASA versus bleeding risks after continuation of ASA during the perioperative period is rather based on the individual experience and personal opinion of the treating physician and/or surgeon.

Apart from severe bleeding episodes complicating the clinical course after an operation, thromboembolic events also account for serious consequences for the individual patient. Presumably, the routinely performed discontinuation of the regular ASA medication in the perioperative setting entails to an increased incidence of thromboembolic events. Retrospective analyses have shown that acute cardiovascular events occur in 2-10% of patients after perioperative discontinuation of ASA, mostly within the first eight days after stopping the long-term anticoagulation regimen.

This is a randomised controlled two-group parallel trial designed to assess the safety and optimize the use of ASA in the perioperative management of patients undergoing general and abdominal surgery. The results of this trial will be used to perform a valid power calculation and to design a confirmative RCT with a higher number of enrolled patients. This may help to clarify the use and potential risk/benefits of perioperative ASA medication in patients undergoing elective surgery.

## Methods and Design

This study has been designed as a prospective randomised controlled, single centre trial with two study arms.

After the study has been approved by the ethics committee of the University of Heidelberg and registration of the protocol at an international registry (ISRCTN45810007) patients on continuous medication with ASA undergoing elective general or abdominal surgery at the Department of General, Visceral and Transplant Surgery, University of Heidelberg, Germany are being screened for participation in this study. Randomisation is conducted using opaque, serially numbered envelopes. The envelopes are being supplied by the Clinical Trial Centre of the Department of Surgery, University of Heidelberg, Germany.

### Participants and Trial population

This study includes patients over 18 years of age who require long-term ASA therapy and are scheduled for the following procedures:

1.) Inguinal Hernia Repair (e.g. Shouldice repair, Lichtenstein's repair, laparoscopic hernia repair)

2.) Cholecystectomy (open and laparoscopic approach)

3.) Elective Colorectal Surgery (right or left hemicolectomy, sigmoid resection, low anterior resection)

Written informed consent is obtained prior to inclusion into the trial.

Patients with ASA medication who were advised to continue antiplatelet therapy throughout the perioperaive period due to medical indication (e.g. shortly after coronary stent implantation, bleeding disorders, etc.) or who were cardiologically evaluated as being a high-risk patient were excluded from this trial. Moreover, emergency procedures, simultaneous participation in another clinical trial, withdrawn or missing written consent and/or a mental condition rendering the subject incapable of understanding the nature, scope, and consequences of the trial lead to exclusion from this study. The eligibility criteria are:

### Inclusion Criteria

- Age equal or greater than 18 years

-Patient has given written informed consent

-Patient is scheduled for elective surgery based on an indication for either inguinal hernia repair, cholecystectomy or colorectal surgery procedures

-Patient treated with ASA on a long-term-medication basis

-Low- or intermediate-risk patient according to cardiological evaluation

### Exclusion Criteria

-High-risk patient according to cardiological evaluation (e.g. necessary perioperative continuation of the ASA application shortly after coronary stent implantation, interfering bleeding disorders etc.)

-Emergency procedure

-Withdrawn or missing written consent

-Simultaneous participation in another clinical trial with interference of intervention and outcome

-Severe psychiatric or neurologic diseases or a mental condition rendering the patient incapable of understanding the nature, scope, and consequences of the trial.

-Concomitant treatment with coumarin-type-anticoagulation or clopidogrel

### Trial interventions

Patients are randomized into one the following two study arms:

Arm 1: Continuation of ASA during the perioperative period

Arm 2: Discontinuation of ASA five days prior to surgery and resumption of ASA intake on postoperative day 5.

### Primary outcomes/secondary outcomes (Table 1)

**Table 1 T1:** Primary and secondary outcomes

**Primary endpoints**	**Definition and assessment of outcomes**
Perioperative thromboembolic event	
Perioperative bleeding complication	*Occurrence of critical blood-loss requiring surgical intervention or the application of coagulation products (FFP, coagulation factors) to normalize the INR*
**Secondary endpoints**	**Definition and assessment of outcomes**
Operation time [min]:	Time from skin incision to placement of last skin staple/suture.
Intraoperative blood loss [ml]:	Blood loss observed from skin incision to placement of last staple/suture.
Duration of postoperative hospital stay [days]:	Time from day of surgery to day of discharge.
Morbidity/	
Surgical complications	
Medical complications	
Peri-/postoperative need for blood/coagulation products	
Re-laparotomy/laparoscopy	Re-operation within the time of index hospitalization respectively within the time of follow-up after the index operation.
In-hospital mortality:	Death due to any reason within the patient's initial hospital stay.
Readmisson	

The primary objective of the present randomised controlled trial is to evaluate the safety of continuous use of ASA during the perioperative period of patients undergoing elective general and abdomina surgery with the ultimate aim to generate high-quality data for the development of evidence-based guidelines on the perioperative use of ASA.

The primary outcome is the incidence of perioperative bleeding episodes and clinically apparent thromboembolic events within 30 days after surgery. Secondary endpoints are the duration of the surgical intervention, intraoperative blood loss, transfusion requirements, length of hospital stay (d), medical and surgical morbidity, and the necessity of readmission.

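### The primary bleeding definition ties its non-surgical trigger to correcting the INR and omits platelets and red cells, so it can miss critical bleeds in a trial of an antiplatelet drug

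*Protocol article*

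**What the plan says.** In the section on primary and secondary outcomes, Table 1 defines the primary bleeding complication as "Occurrence of critical blood-loss requiring surgical intervention or the application of coagulation products (FFP, coagulation factors) to normalize the INR". There are two triggers: surgery, or coagulation products given to correct the INR. The examples in brackets are plasma and clotting factors.

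The text below the table is wider: "The primary outcome is the incidence of perioperative bleeding episodes and clinically apparent thromboembolic events within 30 days after surgery". It carries neither condition. The Abstract (Methods/Design) differs again and speaks of bleeding after surgery.

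Other bleeding information is secondary. Table 1 lists "Peri-/postoperative need for blood/coagulation products", and intraoperative blood loss, which is limited to "Blood loss observed from skin incision to placement of last staple/suture".

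Three further statements bear on the point:
- The Background places the study drug among the antiplatelets: "Antiplatelet agents and in particular acetylsalicylic acid (ASA) were shown to be beneficial".
- The Exclusion Criteria remove patients with "Concomitant treatment with coumarin-type-anticoagulation or clopidogrel".
- The primary objective is to "evaluate the safety of continuous use of ASA during the perioperative period".

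The Sample size section says that the pilot is to supply data for the power calculation of a confirmatory trial.

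**The concern.** The INR reflects plasma clotting factors. ASA impairs platelets, and the patients with the most obvious drug-related reason for a raised INR are excluded. The non-surgical trigger is therefore tied to a laboratory value that the randomised drug is not expected to move. The products more naturally linked to a platelet defect or to blood loss, platelets and red cells, are not triggers.

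Bleeding is the harm to be feared from continuing ASA, and the safety of continuing is the primary question. If real bleeds go unregistered, the primary bleeding rate is too low, any true absolute excess under continuation looks smaller than it is, and the rate handed to the confirmatory trial is too low. Because the table and the text differ, the same data could also yield two different primary bleeding rates.

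**Working it through.** **Step 1: which critical bleeds count.** Applying the wording of Table 1 literally:

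| Management of a critical bleed | Primary event under Table 1? | Covered by the wider text? |
|---|---|---|
| Surgical intervention | Yes | Yes |
| Plasma or clotting factors to correct the INR | Yes | Yes |
| Plasma or clotting factors for bleeding, INR not the reason | Not on the literal wording | Yes |
| Platelets only | No | Yes |
| Red cells only | No | Yes |

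The secondary endpoint names blood products and coagulation products separately. This supports reading the coagulation products of the primary definition as excluding red cells.

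**Step 2: no figure to reproduce.** The documents give no bleeding rate, alpha, power or effect size, and the Sample size section calls the number of patients arbitrary. What follows is illustration on assumed rates.

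**Step 3: effect of incomplete capture.** Inputs:
- n = 52 / 2 = 26 per arm (total from Sample size, equal allocation from the Abstract).
- True bleeding rates p_D (discontinuation) and p_C (continuation): assumed.
- s, the share of true bleeds that the definition registers, the same in both arms: assumed.

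Formulas:
- Registered difference = s × (p_C − p_D).
- Registered ratio = (s × p_C) / (s × p_D) = p_C / p_D, unchanged.
- Expected registered events per arm = 26 × s × p.
- Chance of no registered bleed under continuation = (1 − s × p_C)^26.
- Follow-on trial, per arm, two-sided alpha 0.05, 80% power, no continuity correction, with p1 and p2 the registered rates and p̄ their mean: [1.96 √(2p̄(1−p̄)) + 0.8416 √(p1(1−p1) + p2(1−p2))]² / (p2−p1)².

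Worked example, 10% v 20%, s = 1: [0.9897 + 0.4208]² / 0.01 = 199 per arm.

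| Assumed true rates (D v C) | s | Registered difference | Expected events (D v C) | No registered bleed in 26 continuation patients | Follow-on trial, per arm |
|---|---|---|---|---|---|
| 5% v 10% | 1 | 5 points | 1.3 v 2.6 | 6.5% | 435 |
| 5% v 10% | 0.5 | 2.5 points | 0.65 v 1.3 | 26% | 906 |
| 5% v 10% | 0.25 | 1.25 points | 0.33 v 0.65 | 52% | 1848 |
| 10% v 20% | 1 | 10 points | 2.6 v 5.2 | 0.3% | 199 |
| 10% v 20% | 0.5 | 5 points | 1.3 v 2.6 | 6.5% | 435 |
| 10% v 20% | 0.25 | 2.5 points | 0.65 v 1.3 | 26% | 906 |

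**Step 4: what limits the pilot in any case.** For 10% v 20%, power at 26 per arm is 17% with full capture, 10% at s = 0.5 and 7% at s = 0.25. It is low under every definition.

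**The case against.** The requirement that blood loss be critical shows an intent to count severe events, which is a legitimate choice. The surgical trigger registers a severe bleed whatever its mechanism, and plasma given for an INR that becomes abnormal during a major bleed also counts. Excluding coumarin users does not show that the INR stays normal in critical blood loss. Transfusion need and intraoperative blood loss are still collected, so planners of the next trial could draw on them. The trial is a declared pilot with a descriptive analysis, and no formal safety conclusion rests on a test of this endpoint.

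Much of this stands, and it rules out two stronger readings that a reader might infer:

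- **That the definition cannot register most bleeding.** The documents give neither a bleeding rate nor a split of bleeds by treatment, and the surgical trigger is open to ASA-related bleeds. Only the weaker statement, that bleeds can be missed, is supported.
- **That the definition favours continuation.** This needs a true excess under continuation, which is part of what the trial asks, and missed bleeds that are not concentrated in the discontinuation arm. Even then, with equal capture, the absolute difference is diluted, the ratio is unchanged and nothing is reversed. The text's lower-sounding threshold for thromboembolic events, that they be clinically apparent, does not establish a bias either.

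What the objection does not answer is the INR condition itself. A wish to count only severe bleeds does not justify it: a critical bleed managed with platelets and red cells fails the definition however severe it is. Secondary collection keeps the information but not in the primary rate.

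**Conclusion.** The point holds in a limited form. Table 1 can miss critical bleeds because its non-surgical trigger depends on the INR and leaves out platelets and red cells, and it is narrower than the text that it is meant to define. Both follow from the wording alone.

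The effect on the results is conditional. If continuation raises bleeding and capture is similar in both arms, the absolute excess shrinks in proportion to the captured share, and the bleeding rate available for planning is too low. The true rates and the capture share are assumptions, and the documents do not narrow them.

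In a pilot of 52 with a descriptive analysis, this is a moderate defect. It matters chiefly for the rate that the pilot passes on.

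**What to change.** - Delete the condition that coagulation products be given to correct the INR.
- Define the primary bleeding event as critical blood loss leading to surgical intervention, or to transfusion of red cells, platelets or coagulation products given for bleeding. Take it from the operative and transfusion data already collected.
- Align Table 1, the outcome text below it and the Abstract, so that all three give one definition and one time window.
- Report the present Table 1 definition as a sensitivity analysis.

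The cost is an amendment to the definition. Transfusion need is already a secondary endpoint, so no new type of data is required, though each transfusion must be attributable to bleeding. The downside is that some less severe bleeds, and some transfusions unrelated to ASA, will be counted. The sensitivity analysis shows how much that matters.

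### The only mortality endpoint stops at discharge although the primary outcome runs to day 30, so later deaths are not counted as deaths and the window depends on length of stay

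*Protocol article*

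**What the plan says.** In the protocol article, Table 1 (under Primary outcomes/secondary outcomes) lists in-hospital mortality as a secondary endpoint and defines it as "Death due to any reason within the patient's initial hospital stay". No other mortality endpoint is defined.

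Other outcomes reach further:

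- **Primary outcome:** "The primary outcome is the incidence of perioperative bleeding episodes and clinically apparent thromboembolic events within 30 days after surgery". The abstract gives the same horizon.
- **Re-operation:** the Table 1 row directly above mortality counts "Re-operation within the time of index hospitalization respectively within the time of follow-up after the index operation".
- **Readmission:** listed in Table 1 and in the text; by its nature it happens after discharge.

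Postoperative hospital stay is a separate secondary endpoint, defined as "Time from day of surgery to day of discharge". The text list of secondary endpoints below Table 1 ends with "length of hospital stay (d), medical and surgical morbidity, and the necessity of readmission" and does not mention mortality.

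**The concern.** The stated objective is safety, and death is the most serious harm. Yet death has a shorter window than the primary outcome and than re-operation. A re-operation during a readmission counts; a death during the same readmission does not count as a death.

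The window is also set by something that happens after randomisation. It closes at discharge, and stay is itself an outcome that complications can lengthen. Patients who stay longer are watched longer for death. The eligible operations range from inguinal hernia repair to low anterior resection, so windows can differ widely between patients. If stay differs by arm, the arms are observed for unequal times.

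The pilot is meant to supply data for a confirmatory trial, so a weak mortality definition could be carried into that design.

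**Working it through.** The article states no mortality rate, no length of stay and no figure for this endpoint, so there is nothing of its own to reproduce. The check has two parts: a comparison of windows, which rests on the document, and an illustration of size, which rests on assumptions.

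**1. Windows side by side (Table 1 and the text below it)**

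| Outcome | Counted until |
|---|---|
| Bleeding and thromboembolic events (primary) | day 30 after surgery |
| Re-operation | index stay and follow-up |
| Readmission | after discharge; end not stated |
| Death | discharge from the initial stay |

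Of these four, only death is cut off at discharge.

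**2. What is lost for a death after discharge and before day 30**

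- Clinically apparent thromboembolic event: counted in the primary outcome; its fatal result is not counted as mortality.
- Bleed meeting the Table 1 definition: the same.
- Other, sudden or unexplained death: not counted as a death, and not in the primary outcome unless attributed to one of its components.

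**3. Overlap with the treatment contrast**

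Arm 2 stops ASA five days before surgery, with "resumption of ASA intake on postoperative day 5" (Trial interventions). The Background says that cardiovascular events after stopping occur mostly within eight days. Counted from the stop, that period ends at about postoperative day 8 − 5 = 3. For an assumed discharge on day 2, the full calendar days still off ASA are days 3 and 4. These two days lie outside the mortality window, as do any days off ASA before admission.

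**4. Share of the 30 days covered (assumed stays)**

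Share = stay / 30.

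| Assumed stay (days) | 2 | 3 | 5 | 7 | 10 | 14 |
|---|---|---|---|---|---|---|
| Share | 7% | 10% | 17% | 23% | 33% | 47% |

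**5. Chance of recording any death among 52 patients (assumed 30-day mortality p, constant hazard)**

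30-day window: 1 − (1 − p)^52. In-hospital window with stay L: 1 − (1 − p)^(52 × L/30).

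| p | 30-day window | L = 3 days | L = 10 days |
|---|---|---|---|
| 0.5% | 0.23 | 0.03 | 0.08 |
| 1% | 0.41 | 0.05 | 0.16 |
| 2% | 0.65 | 0.10 | 0.30 |

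At p = 1%, the expected number of deaths over 30 days is 52 × 0.01 = 0.52 for both arms together.

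**6. Effect of unequal stays alone**

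With the same constant daily hazard in both arms and assumed stays of 10 and 7 days, the ratio of in-hospital mortality is about 10/7 = 1.43, with no true difference in risk. The document does not say whether stays differ, or in which direction.

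**The case against.** The strongest reply is that this is a deliberate and common choice of secondary endpoint. It is labelled in-hospital mortality and defined as exactly that, so the article does not contradict itself. The safety question rests on the 30-day primary outcome, which applies regardless of discharge. The trial is a pilot in low- or intermediate-risk elective patients, reported with means, standard deviations, numbers and percentages. No mortality contrast could be interpreted in 52 patients under either window.

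Most of this stands, and it rules out several stronger readings that a reader might infer:

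- **That a fatal thromboembolic event at home disappears from the trial.** If clinically apparent, it is a primary outcome event.
- **That the arm comparison is biased in a known direction.** Bleeding could lengthen stay under continuation, and thromboembolic events could lengthen it under discontinuation. The article supports neither. Stays that differ by operation do not by themselves bias a randomised comparison.
- **That the 7% to 47% is the share of deaths captured.** It is calendar time from assumed stays. If risk is concentrated early, as the Background suggests for events after stopping ASA, the loss for that mechanism is smaller than these shares imply.
- **That a 30-day visit or call already exists.** None is described; the 30-day outcome only implies that some ascertainment takes place.
- **That the text list seriously conflicts with Table 1.** It is a shorter summary. Re-operation can be read as part of surgical morbidity; only mortality is plainly absent.

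The reply does not justify the definition. Death is the one harm explicitly cut off at discharge, in a safety trial that needs information after discharge for its primary outcome. This is a stated definition, not a detail that a condensed article leaves to a fuller document.

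**Conclusion.** The point holds in limited form. As written, deaths between discharge and day 30 are not counted as deaths, and the observation time for death depends on length of stay, itself an endpoint. The loss is the fatal result of events that otherwise reach the primary outcome, plus deaths from other or unclear causes.

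This conclusion rests on the text of Table 1 alone. The size does not: every stay, mortality rate and hazard shape used above is assumed. Under those assumptions the window covers 7% to 47% of the 30 days, and the chance of recording any death falls from 0.23–0.65 to 0.03–0.30. With few deaths expected, the effect on this pilot's results is modest. The definition should be corrected, but it does not undermine the primary analysis.

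**What to change.** - In Table 1, define the endpoint as all-cause mortality from randomisation to 30 days after surgery, for all randomised patients. Starting at randomisation includes deaths before admission, when arm 2 may already be off ASA.
- Keep in-hospital death as an additional descriptive line.
- Add mortality to the text list of secondary endpoints so that it matches Table 1.

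The sample size does not change. Every operated patient is then followed to the same postoperative day whatever the discharge date. The cost is that vital status must be confirmed at day 30 for each of the 52 patients. This should be small, because the 30-day primary outcome already implies some ascertainment after discharge; its form is not described in the article and should be checked in the full protocol.

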#### Sample size

Owing to the lack of data that would allow a valid sample size calculation, the present trial was designed as a randomised controlled pilot trial. A total of fifty-two consecutive patients with continous low-dose medication of ASA, who are scheduled for elective general and abdominal surgery, are enrolled in the present study and randomly allocated to either study arm. This pilot trial generates data for the power calculation of a subsequent RCT with a confirmative design. For the pilot phase of this trial the number of patients to be enrolled was arbitrary defined by the investigators.

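### The primary outcome is tied to surgery although the discontinuation arm stops ASA five days earlier, so on the plain reading about half or more of the withdrawal period named in the Background is not counted

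*Protocol article*

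**What the plan says.** The outcome sentence in the section Primary outcomes/secondary outcomes reads: "The primary outcome is the incidence of perioperative bleeding episodes and clinically apparent thromboembolic events within 30 days after surgery". The abstract (Methods/Design) is worded more narrowly: "The primary outcome is the incidence of postoperative bleeding and cardiovascular events at 30 days after surgery". Table 1 lists a perioperative thromboembolic event and a perioperative bleeding complication as primary endpoints and gives no start date for either.

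Under Trial interventions the second arm is described as: "Arm 2: Discontinuation of ASA five days prior to surgery and resumption of ASA intake on postoperative day 5".

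The Background reports, from retrospective analyses, that "acute cardiovascular events occur in 2-10% of patients after perioperative discontinuation of ASA", and says of their timing: "mostly within the first eight days after stopping the long-term anticoagulation regimen".

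No section says that outcome counting starts at randomisation or on the day ASA is stopped. The Sample size section states that the pilot is to supply data for the power calculation of a later confirmatory trial.

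**The concern.** The contrast between the arms begins when one of them stops ASA, on day -5. The outcome, as worded, is anchored to the operation on day 0. Between those two points only the discontinuation arm is off the drug, and the article's own rationale says that the early days after withdrawal carry most of the risk.

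An infarction or stroke on day -2 in a patient off ASA is the kind of event the trial is meant to detect, yet a count of postoperative events would not include it. The continuation arm has no withdrawal events to lose, so the loss would be mainly one-sided and would make discontinuation look safer on the thromboembolic component. The bleeding component is affected differently: nothing in the article suggests a comparable pre-operative loss of bleeding events. The two harms that the trial sets against each other may therefore be captured unequally, and the understated rate could carry into the design of the next trial.

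**Working it through.** The article gives no figure of its own to reproduce here. The sample size is stated to be arbitrary, with no alpha, power or effect size. The check is therefore date arithmetic, followed by an illustration.

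**Inputs**
- Start of the interruption in the discontinuation arm: five days before surgery (Trial interventions).
- Withdrawal period: first eight days after stopping (Background).
- Event rate after discontinuation: 2-10% (Background).
- Patients: 52 (Sample size), who "are randomised equally to perioperative continuation or discontinuation of ASA", so 52 / 2 = 26 per arm.

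**Step 1: place the eight days on the surgery scale (surgery = day 0)**

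The article does not say whether day -5 is the first day without ASA or the day of the last dose, so both are shown.

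| Convention | Eight days | Before surgery | Share before surgery |
|---|---|---|---|
| First ASA-free day is -5 | -5 to +2 | 5 | 5/8 = 62.5% |
| Last dose on day -5, first ASA-free day is -4 | -4 to +3 | 4 | 4/8 = 50% |

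A count that starts at surgery therefore covers only 3 or 4 of the eight days. These are shares of time, not of events.

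**Step 2: illustration in events**

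Assumptions, none of them given in the documents: all withdrawal events fall in the eight days; they are spread evenly; and the whole 2-10% consists of such events, counted from the stop of ASA.

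Expected events = 26 x rate. Uncounted events = 26 x rate x share before surgery. Recorded rate = rate x (1 - share before surgery).

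| Assumed rate | Expected events in 26 | Uncounted at 5/8 | Recorded rate at 5/8 | Uncounted at 4/8 | Recorded rate at 4/8 |
|---|---|---|---|---|---|
| 2% | 0.52 | 0.52 x 0.625 = 0.33 | 0.75% | 0.52 x 0.5 = 0.26 | 1% |
| 10% | 2.6 | 2.6 x 0.625 = 1.63 | 3.75% | 2.6 x 0.5 = 1.3 | 5% |

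The Background says only that events fall mostly in the eight days. If half of them did, the uncounted numbers would halve. If events cluster around or after the operation, fewer would be missed; if they cluster soon after withdrawal, more would be.

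**The case against.** The strongest reply is that the wording does not exclude the pre-operative days. The outcome sentence and Table 1 say *perioperative*, and the article uses the same word for the whole ASA interruption, which starts five days before surgery. On that usage, the 30 days could fix only the end of the window. This reading is possible, so it cannot be said as fact that the investigators meant to count from surgery onward. But the word is not defined, the only stated window is anchored to surgery, and the abstract calls the bleeding events postoperative. Either the pre-operative days are left out or the sections disagree, and the same correction serves both cases.

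Three stronger readings are tempting and do not stand:

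- **That most of the risk period is lost.** This holds for 5 of 8 days but not for 4 of 8, and the article does not settle which applies.
- **That a known percentage of withdrawal events is missed.** The article does not give the distribution of events within the eight days. Nor does it say when the retrospective analyses began counting, or how much of their 2-10% is due to withdrawal rather than to background or surgical risk.
- **That a patient whose operation is cancelled after an event drops out of the denominator.** No section defines the denominator or the handling of cancelled operations, and a condensed article may leave both to the full protocol.

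It is also fair to say that this is a 52-patient pilot whose described analysis is means, standard deviations, numbers and percentages. With about 26 patients per arm, imprecision in the event rate would outweigh this bias. That lowers the severity but does not justify a window that starts after the exposure.

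**Conclusion.** The point holds as a misaligned and incompletely defined outcome window. Followed as written, the primary outcome can miss thromboembolic events in the 4 or 5 days off ASA before surgery, out of the eight days that the Background singles out. Any loss from withdrawal would fall mainly in the discontinuation arm, and would understate its thromboembolic rate and the rate handed to the confirmatory trial.

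The direction is clear and the size is not. The figure of about 0.3 to 1.6 uncounted events is the 5-of-8 case and depends on the assumptions in the working; on the 4-of-8 convention it is about 0.26 to 1.3. It should be cited only as an illustration. A reader might infer that the trial's comparison is demonstrably biased by a large amount; the documents do not support that. The correction is well worth making, but the trial does not stand or fall by it.

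**What to change.** Redefine the window for the primary outcome in both arms: thromboembolic and bleeding events count from the scheduled ASA stop day (day -5, with the same calendar point used in the continuation arm) to 30 days after surgery. Randomisation could serve as the start instead. However, the article does not say how long before surgery randomisation takes place, so the scheduled stop day is the cleaner common origin if randomisation is earlier.

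State that events in randomised patients before the planned operation, or instead of it, are included. Where no operation takes place, the window can close 30 days after the planned date. Tabulate pre-operative and postoperative events separately, so that the later power calculation can use either rate. Use the same wording in the abstract, the outcome sentence and Table 1, and define *perioperative* there.

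The cost is a short amendment and one question at admission about events since the stop day. A few pre-operative events unrelated to the allocation will be counted in both arms; the separate tabulation keeps them visible. No treatment rule changes, and the sample size stays at 52.
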